### Outcome measures

These measurements are made by an interviewer blind to group allocation.

*Primary outcome measure* (baseline, 3, 6 and 12 months):
Cardiorespiratory functional capacity, as assessed using a 400-m walk testChanges in health-related quality of life, as assessed using the 36-item Short-Form Health Survey (SF-36) and disease-specific questionnaires: the European Organization for the Research and Treatment of Cancer Quality of Life Questionnaire (EORTC QLQ-C30) in patients with cancer; and the COPD Assessment Test (CAT) and Chronic Respiratory Disease Questionnaire (CRQ) in patients with COPD.

*Secondary outcome measures* (baseline, 3, 6 and 12 months):
Muscle strength test measured by the handgrip strength and sit-and-stand testsThresholds for lactate (LT1 and MLSS), HR, and accelerometer activity counts for tailoring the exercises, determined in submaximal walking or running tests. For detecting LT1, a test will be carried out on a 20-m track. This will be an incremental test combining 2-min active period and 1-min rest period. To help the participant adjust their speed in each 2-min period, red markers will be placed every 5 m on the floor and the wall on both sides and two large cones on the floor at each end of the track. Participants will be asked to reach the next red markers each time they hear a beep, continually adjusting their speed but without stopping; that is, they should go faster or more slowly seeking to pass each set of markers at the time of the corresponding beep. The speed will start at 2.4 km/h in the first stage; and will increase by 0.61 km/h each stage [40]. At the end of each stage, the following will be recorded: HR, Rating of Perceived Exertion and lactate concentration, by taking a blood sample from each earlobe to find the minimum lactate equivalent (LEmin) above which the lactate concentration starts to increase exponentially. Hence, the aerobic threshold is defined as the intensity of exercise (speed) at which the lowest recorded lactate level is followed by changes ≥0.1 mmol/L in the next stage and > 0.2 mmol/L the one after [25]. The test will be stopped if the participant becomes exhausted or lactate levels exceed 3 mmol/L.

To identify MLSS, another test will be performed a week after the incremental lactate test to identify the corresponding lactate threshold. Based on certain parameters from this progressive test, detailed below, it has been shown to be possible to estimate the speed at which an individual reaches the MLSS accurately (estimates accounting for 86% of the variance in MLSS with a standard error of the estimate of 0.385 km/h and the difference between the estimated value of MLSS and the true value lying between − 0.77 and 0.81 km/h 95% of the time) [25].

For assessing the MLSS, the patient should return to the health centre where the measurements are taken 1 week later. The infrastructure required is the same as for the incremental lactate test; all that changes is the protocol. An audio recording will be made with two blocks of 10 min separated by a 2-min recovery period, at an MLSS speed estimated using the results obtained in the incremental lactate test and the following equation: MLSS = 3.408 + (1.094·LEmin+ 1 mM) – (0.036·age – (0.013· LEmin HR)) [25].
Physical activity performed. For this, each participant will be fitted with an Actigraph wGT3X-BT accelerometer on their right hip at the level of the iliac crest and an HR monitor band (Polar OH1). They should wear these monitors for a week and complete a daily record of their activity, to monitor activity counts during different intensities of activity. To analyse these data, we will assess the activity counts, which correlated with LT1 during the incremental test, and thereby be able to assess their weekly physical activity based on personal activity count thresholds.Body composition (OMROM body fat percentage), body mass index and abdominal circumference, estimated cardiovascular risk and the onset of any cardiovascular eventsPsychological changes assessed using Goldberg’s 12-item General Health Questionnaire (GHQ-12) and the Duke Social Support IndexIn addition, in the case of schizophrenia, changes in mental state assessed using the Positive and Negative Syndrome Scale (PANSS), and the severity of the patient’s condition and changes therein during the course of the programme assessed using the Clinical Global Impression (CGI) and the Global Assessment of Functioning (GAF) scaleLipid profile, as well as levels of C-reactive protein, glucose, insulin and specific exercise-related parameters: adiponectin, BDNF in participants with schizophrenia, TNF-α in those with cancer and Il-1 and Il-6 in those who have COPD or are transplant recipients (at baseline and 3 months).Potential predictive, modifying and confounding factors: sex, age, comorbidities (Adjusted Clinical Groups Case-Mix System), risk factors, socioeconomic status, drug treatments and characteristics of each chronic condition.

### Adverse events

Provisional analysis of the data is to be performed by an independent committee to monitor safety. This committee will define indicators in relation to mortality, hospital admissions and cardiac decompensation events, having independent access to the necessary data. Composed of people who are independent of the body in charge of the management of the study and of the researchers and blind to patient group allocation, the committee will review the data every quarter and make recommendations to the team leading the project as to whether the study should be interrupted.

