### Randomisation

Once informed consent has been obtained and baseline measurements have been taken, patients will be randomised blindly and centrally to either the EG or PVS group, stratified by illness type, at the coordinating centre, the Primary care Research Unit of Bizkaia of the Biocruces Bizkaia Health Research Institute. The randomization will be performed using computer-generated random numbers in a 1:1 ratio, stratified by illness type, with a block size of 4 or 6. (Fig. 1).

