### Sample size

We expect to recruit a total of 370 patients over 2 years; with a loss to follow-up (including deaths) of 30%, this would provide the study with a power of over 90% to detect differences between the two comparison groups in the primary outcome variable (400-m walk completion time) of at least 6 s after 3 months, 12 s after 6 months and 24 s after 12 months of follow-up as significant (alpha = 0.05), assuming a linear increase in the impact of the exercise over time, a standard deviation of 40 s and intra-patient correlation of 0.6. These differences are less than those found in previous studies.

Regarding the quality of life outcome variable, we would have a power of 90% to detect differences between the two groups of 2.5 points at 3 months, 5 points at 6 months and 10 points at 12 months as significant (alpha = 0.05), for all the dimensions of the SF-36 questionnaire, except for physical and emotional roles (80% power) [40].

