### Limitations

The structure of the study makes it impossible to blind the participants or the interveners; however, blind outcome assessors will be used. The monitoring of this intervention and data collection is complex, and therefore, data will be collected using several appropriate quality control processes, and efforts will be made to ensure standardization of the intervention. In addition, to avoid contamination of the control group, interveners will be trained, and a pilot study will also be carried out.

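### The safety committee that advises on interrupting the trial is blind to allocation, with no stated way to learn which arm carries an excess of events

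*Protocol article*

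**What the plan says.** The Adverse events section assigns safety monitoring to an independent body: "Provisional analysis of the data is to be performed by an independent committee to monitor safety". Its indicators and its data access are given in one sentence: "This committee will define indicators in relation to mortality, hospital admissions and cardiac decompensation events, having independent access to the necessary data". Its members are independent of the study's management and of the researchers. They are also "blind to patient group allocation, the committee will review the data every quarter and make recommendations", and the recommendation concerns interruption: "make recommendations to the team leading the project as to whether the study should be interrupted".

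Elsewhere, Study design calls the trial open-label, and Limitations says: "The structure of the study makes it impossible to blind the participants or the interveners; however, blind outcome assessors will be used". Sample size plans 370 patients with 30% loss to follow-up, a figure that includes deaths but does not separate them. Randomisation is 1:1, stratified by illness.

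The article does not mention coded arms, tables by arm or a procedure for opening the allocation. It gives no expected rate of death, admission or cardiac decompensation, overall or for any of the four illnesses.

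**The concern.** Whether the exercise programme causes harm is a question about the difference between arms. The supervised exercise is given in one arm only; the reference arm receives lifestyle advice. The population includes stage IV solid cancer on chemotherapy and COPD with a BODE index of 3 to 7, so some deaths and admissions will come from the illness itself. A body that does not know allocation may be unable to separate those events from events due to the programme.

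Two errors are at stake. An excess in the exercise arm could be missed, or the committee could advise interruption because of a rate that is the same in both arms. The blinding also protects little here. Participants and interveners already know the allocation, and protection of the outcome measurements rests on the blinded assessors, a role the article does not give to the committee.

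**Working it through.** The plan states no safety figure, so there is none to reproduce. The check takes each reading of the blinding in turn.

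**Inputs from the article.** N = 370 (Sample size) at 1:1 (Randomisation), so 370 / 2 = 185 per arm. Expected loss is 0.30 × 370 = 111 patients, with deaths included but not counted separately.

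**Assumed inputs.** Event rates by arm, because the article gives none. The main illustration is 10% v 20%; 5% v 10% and 15% v 30% show the range.

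**Reading 1: pooled data.** The pooled count fixes only the sum of the two arms.

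| Assumed rates (reference v exercise) | Expected events | Total | Pooled rate |
|---|---|---|---|
| 15% v 15% | 27.75 + 27.75 | 55.5 | 15% |
| 10% v 20% | 18.5 + 37 | 55.5 | 15% |
| 20% v 10% | 37 + 18.5 | 55.5 | 15% |

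No effect, harm and benefit give the same total.

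A pooled rate can raise an alarm only against a known background rate. Suppose the background were known to be exactly 10%. A one-sample test of a true pooled 15% in 370 patients has

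z = [0.05 − 1.96 × √(0.10 × 0.90 / 370)] / √(0.15 × 0.85 / 370) = (0.05 − 0.0306) / 0.0186 ≈ 1.05, which gives power of about 85%.

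So pooled review is not powerless in principle. But the alarm would sound about as often for a balanced 15% v 15% as for 10% v 20%, and the article supplies no background rate.

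**Reading 2: coded arms A and B.** The committee would see, for example, 18.5 v 37 expected events and could test the difference. With the pooled null variance, two-sided 0.05 and a single look:

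z = [|p₁ − p₂| − 1.96 × √(2p̄(1 − p̄)/n)] / √([p₁(1 − p₁) + p₂(1 − p₂)]/n)

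For 10% v 20% and n = 185: (0.10 − 0.0728) / 0.0368 ≈ 0.74, power 77%.

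| Assumed rates | n per arm | Power |
|---|---|---|
| 5% v 10% | 185 | 45% |
| 10% v 20% | 185 | 77% |
| 15% v 30% | 185 | 94% |
| 10% v 20% | 92 (about half recruitment) | 48% |

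These powers are for a difference in either direction. Until the code is opened, 10% v 20% and 20% v 10% look alike, so an excess under exercise cannot be told from a benefit of exercise.

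**Limits of these figures.** They assume one look and complete event follow-up. Review is quarterly and recruitment takes two years, so at a real interim look fewer patients would have full follow-up and power would be lower. The figures show what the arm label adds; they do not predict how the committee would perform.

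**The case against.** The strongest reply is that the article never says the data are pooled. Blind to allocation also fits coded arms. The committee performs the analysis and has its own access to the data it needs, which could be read as allowing it to obtain the allocation. A reader might infer that the committee is unable to detect harm at all, or that harm is bound to go unnoticed. The text does not support that: under coded arms an imbalance is visible, and a single event, such as one during a supervised session, may reveal its arm.

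Nor does the article show that background event rates are high. It gives no rates, requires an ECOG status of at most 1 for solid cancer and stable disease for COPD, and 100 of the 370 patients have schizophrenia.

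It can also be said that report format and unblinding procedure belong in a committee charter or the full protocol, which a journal article need not repeat. Their absence alone is not the point here.

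What remains is the blinding, which is a stated rule and not an omission. On either reading, a committee that follows it literally lacks the direction of any excess. If the access clause is meant to override the blinding, the two statements conflict and need to be reconciled.

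**Conclusion.** The point holds in a limited form. The committee is asked to advise each quarter on interruption while blind to allocation, and the article states no way for it to learn which arm is which. With pooled data it cannot detect an imbalance, and it has no stated background rate to judge the total against. With coded arms it can detect an imbalance but not attribute it to the exercise arm. A harm signal could therefore be missed, or a balanced rate misread.

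The ambiguity of a pooled total does not depend on the rates chosen. The 15% example and the powers of 45% to 94% at full recruitment do: they rest on assumed rates, a single look and full follow-up. No figure in the article is contradicted. The change is worth making because it concerns participant safety and costs little.

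**What to change.** Amend the Adverse events section to state that:

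- the committee receives confidential closed tables of deaths, hospital admissions and cardiac decompensation by arm, coded A/B, overall and by illness;
- it may open the code on request;
- its independent access to data is to be read consistently with these two provisions;
- investigators and outcome assessors remain blind to the comparative tables.

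By illness the tables will be small (solid cancer, COPD and schizophrenia 100 / 2 = 50 per arm; blood cancer 70 / 2 = 35), so they are descriptive. No stopping threshold is proposed here.

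The cost is a change of wording and an arm column in the data already reviewed each quarter. The downside is that arm-level safety data must be kept confidential within the committee.

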### Follow-up period

One year from the beginning of the intervention.

### Sample size

We expect to recruit a total of 370 patients over 2 years; with a loss to follow-up (including deaths) of 30%, this would provide the study with a power of over 90% to detect differences between the two comparison groups in the primary outcome variable (400-m walk completion time) of at least 6 s after 3 months, 12 s after 6 months and 24 s after 12 months of follow-up as significant (alpha = 0.05), assuming a linear increase in the impact of the exercise over time, a standard deviation of 40 s and intra-patient correlation of 0.6. These differences are less than those found in previous studies.

Regarding the quality of life outcome variable, we would have a power of 90% to detect differences between the two groups of 2.5 points at 3 months, 5 points at 6 months and 10 points at 12 months as significant (alpha = 0.05), for all the dimensions of the SF-36 questionnaire, except for physical and emotional roles (80% power) [40].

### Qualitative evaluation

The knowledge gained from the qualitative evaluation is essential for the designing of a tailored implementation strategy, addressing any organisational and professional barriers that may hinder the adoption of the EfiKroniK programme under routine conditions. This evaluation is to be based on discussion groups exploring the perception of the patients involved in the study to identify barriers that threaten the feasibility of the intervention as well as facilitators of continuation, adherence, adoption, sustainability and suitability of the EfiKroniK programme. We will hold discussion groups of 5 to 8 people to obtain a broad and heterogeneous perspective of the EfiKroniK programme.

These sessions will be audio recorded, transcribed and analysed. Further, the moderator and the observer will take written notes during the fieldwork to complement and triangulate the information recorded. The analysis will be based on theory based and guided by the Consolidated Framework for Implementation Research (CFIR) theoretical implementation framework which comprises 39 constructs classified into 5 domains: intervention characteristics, outer setting, inner setting, characteristics of individuals and process of implementation [41]. We will perform two types of interpretation: inductive and deductive. First, the inductive analysis will follow a thematic analysis by identifying patterns of meaning, based on grounded theory, applying the following strategies: open coding and development of initial categories; “memoing” to capture ideas and reflections of the interviewer and the research team as they evolve over the course of the study; and interaction diagrams and discussion sessions to bring together all the details and help to make sense of the data in relation to the emerging theory and conceptual maps. Secondly, the deductive analysis will consist of the identification of patterns of meaning related to the CFIR constructs, classifying the elements of the discourse generated into the categories of the theoretical framework.

### Statistical analysis

The statistical analysis will be performed on an intention-to-treat basis, comparing changes observed from baseline throughout the year of follow-up in participants assigned the EG and PVS group, adjusting for baseline, using mixed-effect analysis of covariance (linear for continuous outcomes and logistic for dichotomous outcomes). The effect of time on the repeated measures in each participant will be estimated and the hypothesis of significantly different (*p* < 0.05) changes in the EG and PVS group will be tested, assessing a treatment group-time interaction term. These models will include an additional effect characteristic of each group and the interaction between the conditions and the effect of the intervention (GE/PVS). The comparisons will be adjusted for potential confounders. The aforementioned effects will be considered fixed and patients and primary care centres will be included as random effects in the intercept, time slope and effect of the programme. Models will be simplified with backward and forward selection using Likelihood ratio tests (selection criteria, *p* < 0.05). A sensitivity analysis will be performed including/excluding outliers. Based on these models, the effect attributable to the intervention will be estimated, calculating the mean differences between groups estimated at each of the follow-up points (adjusted odds ratios for dichotomous outcome variables) and 95% confidence intervals. Before such analysis, potential interaction effects between the specific illness group of the participant and the effect of the interaction would have been ruled out. Regarding missing values, these longitudinal mixed effect models are one of the best approaches for managing missing data. Analysis will be performed by pre-established groups to test hypotheses that the programme is more effective in patients with mental illness, young people, males, those with a high socioeconomic status, less advanced stages of illness and those with certain comorbidities, evaluating an interaction term between these covariates and the intervention (*p* < 0.005). An analysis will also be carried out by protocol, considering the actual dose of physical activity to which each participant has been exposed. Finally, the cost-effectiveness and incremental cost-utility ratios and their confidence intervals will be estimated using resampling techniques (bootstrapping) and a sensitivity analysis will be performed, changing the assumptions of the analysis. The statistical analysis will be performed with SAS and R packages. No imputation method will be used to handle missing data since longitudinal mixed models based on maximum likelihood estimation are more appropriate to deal with missing data [42] than common imputation methods such as last observation carried forward, complete case analysis or other possible forms of imputation.

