### Protocol for the EfiKroniK group

First phase: the EfiKroniK group are to participate in an innovative physical exercise programme supervised by fitness and health professionals, ensuring patient safety and adjusting the intensity of the exercise to each patient. In this phase, patients are to develop the skills necessary to become an expert regarding the ideal dose of exercise for them. It consists of 36 sessions of exercise of progressively increasing intensity and tailored to the physical condition of each patient, assessed based on metabolic thresholds. Two sessions a week are to be performed in the laboratory, combining aerobic and strength exercises with stretching, under the supervision of fitness and health professionals and one session a week independently near the health centre, monitored with an HR monitor programmed by the fitness and health professionals. In addition to HR measured with the monitor, exercise is monitored with the modified Borg Rating of Perceived Exertion Scale [35] and the appearance of any symptoms.

Second phase: In this phase, patients are to work independently following a physical exercise programme similar to that of the first phase, taking advantage of resources in the community. To make this feasible, patients are to have been trained during the first phase in the type of exercise and appropriate intensity (Borg Scale, HR monitor, symptoms), and at the end of the 3-month training programme, we will contact individuals who can provide support in the community.

We will calculate the real dose of physical exercise each person has been exposed to: cumulative metabolic equivalent (MET)*h/week and time spent doing moderate and/or vigorous intensity of exercise and intensity of exercise under supervision based on the percentage of heart rate reserve (HRR).

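### The group-by-time interaction named as the hypothesis test asks, in a baseline-adjusted model, whether the benefit changes after month 3 rather than whether there is one; the stated power belongs to that linear trend

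*Protocol article*

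**What the plan says.** The Statistical analysis section compares change over the year between the EfiKroniK group (EG) and the healthy-lifestyle reference group (PVS). It uses a mixed-effect analysis of covariance adjusted for baseline. The hypothesis that "changes in the EG and PVS group will be tested, assessing a treatment group-time interaction term" is the only statement of which term decides the question. The section also promises adjusted group differences with 95% confidence intervals at each follow-up point, and simplifies the models by likelihood ratio tests at p < 0.05.

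The Sample size section claims a "power of over 90% to detect differences between the two comparison groups" in 400-m walk time of "at least 6 s after 3 months, 12 s after 6 months and 24 s after 12 months of follow-up", "assuming a linear increase in the impact of the exercise over time, a standard deviation of 40 s and intra-patient correlation of 0.6". The SF-36 differences (2.5, 5 and 10 points) follow the same straight line.

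The Protocol for the EfiKroniK group section describes a supervised phase of 3 months. After that: "In this phase, patients are to work independently following a physical exercise programme similar to that of the first phase".

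**The concern.** In an analysis of covariance the baseline value sits on the right-hand side, leaving months 3, 6 and 12 as responses. The group main effect carries the benefit, and the group-by-time term carries only its change between visits. A programme that gains its whole benefit by month 3 and keeps it satisfies the null hypothesis of the declared test exactly. A programme whose benefit fades can reject that null, with the slope against it.

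The design makes a plateau or a fade a realistic pattern: supervision stops at month 3, whereas the power assumption has the effect quadruple from 6 to 24 s after that point. At stake is whether an effective programme could fail its own primary test, and whether readers take the power figure to cover the early differences listed beside it.

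**Working it through.** **Inputs.** From Sample size: 370 patients, 30% loss, SD 40 s, within-patient correlation 0.6, alpha 0.05, differences 6/12/24 s. From Randomisation: 1:1 allocation. Hence 370 × 0.7 = 259 patients, or n = 129.5 per arm. Assumed here: two-sided alpha, compound symmetry, and the same 259 patients at every visit. Power = Φ(|z| − 1.96) + Φ(−|z| − 1.96).

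**Reproducing the plan's figure (baseline as covariate, linear time).** Months 3, 6 and 12 have mean 7, so Sxx = 16 + 1 + 25 = 42. Conditioning on baseline subtracts a constant from every variance and covariance and leaves the slope variance unchanged.
- SE of the slope difference = √[2 × 1600 × (1 − 0.6) / (129.5 × 42)] = 0.485 s/month.
- 6/12/24 s is 2 s/month; z = 2/0.485 = 4.12; power 98.5%. With categorical time (2 df) it is 96.7%.

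The claim of over 90% therefore stands for the linear trend.

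**Other shapes, same test.**
- Constant 12 s or constant 24 s: slope 0, power 5.0% with 1 or 2 df. Simulation of the slope test for the 24 s case gave 4.95%.
- Fading 24/18/12 s: slope = (−4×24 − 1×18 + 5×12)/42 = −1.286 s/month; z = −2.65; power 75.5%, in the unfavourable direction.
- Change from month 3 to month 12 needed for 90% power on the slope: 9 × 0.485 × (1.96 + 1.28) ≈ 14 s.

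**Alternative model (baseline as a month-0 response).** Months 0, 3, 6 and 12 have mean 5.25; Sxx = 78.75; SE = √[2 × 640 / (129.5 × 78.75)] = 0.354 s/month.

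| True difference at 3/6/12 months | Fitted slope (s/month) | Power, linear time | Power, categorical time (3 df) |
|---|---|---|---|
| 24/24/24 s | 1.6 | 99.5% | >99.9% |
| 12/12/12 s | 0.8 | 62% | 80% |
| 24/12/6 s | −0.06 | 5% | 99.9% |

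In this model only, a linear fit misreports a constant 12 s: 9 + 0.8 × (t − 5.25) gives 7.2, 9.6 and 14.4 s at months 3, 6 and 12. In the covariate model a linear fit returns 12 s at each visit.

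**Tests that ask whether there is a benefit (baseline as covariate).**
- Average over three visits: variance = 1600 × (1 + 2×0.6)/3 − 1600 × 0.36 = 597.3; SE = √(2 × 597.3/129.5) = 3.04 s. Linear 6/12/24 s averages 14 s: z = 4.61, power 99.6%. Constant 12 s: z = 3.95, power 97.7%.
- Single visit: residual SD = 40 × √(1 − 0.36) = 32 s; SE = 32 × √(2/129.5) = 3.98 s. Power is 33% for 6 s at month 3, 85.5% for 12 s at month 6 and over 99% for 24 s at month 12.

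**The case against.** The best counter-argument is that the text does not fix the covariate model beyond doubt. The same section speaks of change from baseline and of a random time slope, the Outcome measures section lists baseline among the measurement times, and the assumed effect is a line through zero at month 0. If baseline is a response, a large plateau is detected easily. This stands, and the 5% figure must carry that condition. It does not remove the problem: a 12 s plateau still falls to 62% or 80%, and a 24/12/6 s benefit is almost invisible to a linear time term. The low figure for that fading pattern does depend on linear coding, which the article does not settle.

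Second, the promised visit-by-visit differences with confidence intervals would show a sustained benefit, and would show the direction of a fading one. This also stands: the effect would be estimated and reported. Model simplification might also drop a null interaction and leave the group effect. But the article names neither that effect nor any visit difference as the test of the hypothesis, and reaching one only after data-driven selection is not the same as declaring it.

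Third, the linear assumption is disclosed, and no figure in the document says that a plateau is more likely than growth. Both points are fair. The argument needs only that a plateau or fade is possible, which a supervised phase ending at month 3 makes reasonable.

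**Conclusion.** The concern holds for the declared test and for the wording of the power statement. On the plain reading of a baseline-adjusted analysis of covariance, the interaction has 5% power for any constant benefit, against about 98% for the averaged adjusted difference when the true benefit is a constant 12 s.

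A reader might infer three stronger things that the document does not support:
- That the trial has 5% power for a plateau under any model. It does not if baseline is a month-0 response.
- That the power was miscalculated. It reproduces at 98.5%; the fault is that power for a trend is presented as power for the listed visit differences.
- That the power holds only for exactly linear growth. About 14 s of change after month 3 gives 90% on the slope, whatever the earlier gain.

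The figures rest on two-sided alpha, compound symmetry and 129.5 patients per arm at all visits. Adding random slopes lowers the linear-trend power (to 90.5% at a slope SD of 3 s/month) and leaves the plateau result at 5%. The same reasoning applies to the SF-36, but no SD is given there, so no figure is offered.

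**What to change.** In Statistical analysis:
- State that baseline is a covariate and code visit as categorical.
- Name as the primary test the baseline- and illness-adjusted EG minus PVS difference, either averaged over 3, 6 and 12 months or at one named visit. Either is acceptable if fixed in advance.
- Keep the group-by-time term as a secondary description of durability, and do not let model selection decide which contrast is tested.

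In Sample size:
- Say that the figure of over 90% refers to the linear trend, and restate power for the chosen contrast. For the average over visits this is 99.6% under the assumed linear growth and about 98% for a constant 12 s. If a single visit is named, use the single-visit power for that visit.

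The cost is wording in two sections, with no extra patients, visits or data. If growth really is linear, the averaged contrast gives up nothing against the slope test (99.6% against 98.5%). The one unwelcome consequence is that the plan would no longer appear to promise high power for 6 s at month 3.
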